### Interventions

Participants will receive real or sham catgut implantation at acupoints once per 2 weeks. Each patient will have 4 treatment weeks and 12 weeks of follow-up. The interventions are designed according to the documentary records in ancient books and in recent Traditional Chinese Medicine journals. The protocol is developed in consensus with Chinese acupuncturists and acupuncture experts, and is consistent with both the STRICTA (Standards for Reporting Interventions in Controlled Trials of Acupuncture) guidelines for the performance of acupuncture studies [12] and the guidelines for clinical research on acupuncture (WHO Regional Publication, Western Pacific Series No.15, 1995). In our pilot study, five acupoints were used for catgut implantation and the efficacy was similar between the catgut implantation in the acupoints group and the intranasal glucocorticosteroids group. In this trial, the same acupoints will be chosen in both the real and sham treatments. All the treatments will be performed by the same registered acupuncturists to ensure participant blinding and consistency of treatment.

#### Rationale for the selection of acupoints

For the first 2 weeks of treatment, three acupoints are to be used for each patient. They are Yingxiang (LI20), Yintang(EX-HN3), and Hegu(LI4). For the second 2 weeks of treatment, Zusanli(ST36) and Quchi(LI11) will be chosen (Figure 2).

**Figure 2 F2:**
[figure not shown]
**Locations of acupoints ****(****for both real treatment group and sham**-**controlled group****).** Yintang(EX-HN3), yingxiang (LI20), and Zusanli (ST36) are chosen in the first two weeks of treatment. Hegu(LI4) and Quchi (LI11) will be punctured in the second two weeks of treatment.

The traditional acupuncture theories state that AR is in close correlation with the Taiyin lung meridian of hand and Yangming large intestine meridian of hand. Therefore, it is reasonable that the acupoints corresponding to the lung meridian and the large intestine meridian would be the most effective acupoints in treating AR. Furthermore, the traditional acupuncture theory maintains that special points convey special therapeutic effects. Thus, the most frequently used specific acupoints for these two meridians would be selected in this trial according to a previous review of ancient and modern literature.

In traditional Chinese medicine, the nose is an orifice with lucid Yang. Yingxiang and Yintang are on the median line of face. Lucid Yang is confluent at these acupoints. These two acupoints plays an important role in clearing nasal passage. In addition, Yingxiang is considered a specific point on Yangming large intestine meridian of hand. Hegu is the source-point of the large intestine meridian. Based on the theory of the lung and the large intestine being interior-exteriorly related, Yingxiang and Hegu are important acupoints for facial features. Yintang is an extraordinary point. The three acupoints could be used together for improving lung air (qi) deficiency syndrome. In our previous trial, it has been suggested that symptoms of AR could be effectively alleviated by embedding catgut at these three acupoints.

Zusanli (ST36) and Quchi(LI11) are sea points of Yangming large intestine meridian of hand and Yangming stomach meridian of foot. The ancient Chinese believed that Yangming is a meridian abundant of blood and Qi and is the acquired foundation. Zusanli and Quchi will be used to fortify the spleen and replenish lung qi. By reinforcing earth to generate metal and by regulating asthenia-cold in the remission stage of AR, recurrence rate of this disease might be reduced.

#### Sham-controlled group

In the control group, the same acupoints are to be punctured with the same acupuncture needles and same length and angle according to standard techniques. The only difference between these two groups is that catgut would not be embedded into the acupoints in the sham-controlled group. Because of mild swollen tissue at acupoints immediately after puncture and lack of previous experiences for this therapy, the patients will not know whether catgut has been embedded into the acupoints. To ensure the blinding manner, acupuncturists are instructed not to communicate with the participants of whole treatment procedures.

#### Standard protocol for catgut implantation at acupoints

Only pre-sterilized disposable needles (9#, Hanjiang Guoxiang Medical Appliance Factory, Yangzhou, China) and catguts (000, Pudong Jinhuan Medical Products Co. Lit, Shanghai, China)are used in the trial. For Yintang (EX-HN3), the needle is to be inserted with a depth of 1.0 cm, downward to the nose in a horizontal direction with respect to the shin. For Yingxiang (IL20), the penetration is 2.0 cm, in an oblique direction along the nasolabial sulcus towards the root of nose with respect to the skin. For Hegu, Zusanli, and Quchi, the penetration is 2.5 cm, in perpendicular direction with respect to the skin (Table 1). Twirling, lifting, and thrusting of the needle do not need to be performed. Both groups will receive one session of catgut implantation every 2 weeks for 4 weeks. Subjects will be advised to lie on a supine position. Pulse rate, blood pressure, and oxygen saturation are to be monitored routinely during the procedure as a precautionary measure. In both groups, pre-injection swabs with 75% alcohol and dry sterile cotton wool are to be used when withdrawing the needles. Before the puncture, it is advised to inject 0.5% Lidocaine of about 0.2 to 0.4 mL for each acupoint to alleviate the pain caused by inserting the needle. After treatment, the skin of the acupoints is prohibited to touch water or any cosmetics for 3 days.

**Table 1 T1:** Acupoints and manipulation for both real and sham catgut implantation group

**Time**	**Acupoints**	**Angle and direction**	**Depth ****(cm)**
First week of treatment	Yintang(EX-HN3)(unilateral)	Downward to the nose in a horizontal direction with respect to the shin	1.0
	Yingxiang(LI20)(both)	In an oblique direction along the nasolabial sulcus towards the root of nose with respect to the skin	2.0
	Hegu(LI4)(both)	In perpendicular direction with respect to the skin	2.5
Second week of treatment	Zusanli(ST36)	In perpendicular direction with respect to the skin	2.5
	Quchi(IL11) (both)	In perpendicular direction with respect to the skin	2.5

The needle used for catgut implantation is similar to a kind of trocar. It is made up of two parts: the internal stylet and the external cannula with sharp pinhead which assures the cannula could puncture into the skin (Figure 3). In real catgut embedding, the internal stylet should be withdrawn from the cannula for about 1.5 cm at first. Then a catgut with the length of 2 to 3 mm will be put into the cannula from the side of pinhead. When the needle has been inserted into the acupoints with the correct depth, the catgut will be pushed into the tissue of the acupoint by the stylet. For the control group, the whole therapeutic procedure is the same as the real group except that the catgut is not present in the cannula. Patients in the control group will receive only the stimulus of needling but not of the catgut implantation.

**Figure 3 F3:**
[figure not shown]
Needle for catgut implantation at acupoints.

All real and sham catgut implantation are to be performed by the same acupuncturist consistently throughout the study. The acupuncturists should have undergone at least 8 years of acupuncture training and be qualified TCM doctors.

In both groups, patients are permitted to use chlorphenyramine when needed. The use of chlorphenyramine (dosage, frequency, and period of treatment) will be recorded as relief medicine scores.

### Outcome measurements

#### Primary outcome

The primary outcome measures will be the severity of the AR symptoms assessed by (VAS) [9] and the RQLQ [10,11]. In VAS, the severity of the combination of the nasal symptoms will be subjectively rated by the study patients on the scale. The severity of symptoms can be divided into mild, moderate, or severe based on the total severity VAS score (0 to 10 cm: mild, VAS 0–3; moderate, VAS 3.1-7; severe, VAS 7.1-10). VAS scores will be recorded every 2 weeks during the whole trial. Influence of AR on QOL will be measured by questionnaire every 4 weeks: at baseline, at the end of treatment, during the follow-up period, and at the end of follow-up period (a total of five times). Both the scores of VAS and RQLQ questionnaire will be blindly assessed.

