**Methods and design:**

This study compares real *versus* sham catgut implantation at acupoints in 242 patients with a history of PER or IAR and with a positive skin prick test (SPT). The trial will be conducted in the Teaching Hospital of Chengdu University of Traditional Chinese Medicine. In the study, patients will be randomly assigned by computer-generated randomization list into two groups and assessed prior to treatment. Then, they will receive two sessions of treatments (once per 2 weeks) for 4 consecutive weeks and have a follow-up phase of 12 weeks. The administration of catgut implantation (or sham-control) at acupoints follows the guidelines for clinical research on acupuncture (WHO Regional Publication, Western Pacific Series No.15, 1995), and is performed double-blindly by a well-trained physician in acupuncture. The main outcome measures include the primary and secondary indicators. Primary indicators are subjective symptoms scores evaluated by visual analogue scales (VAS) and Rhinoconjunctivitis Quality of Life Questionnaires (RQLQ). The secondary indicators are the results of laboratory examinations, such as serum allergen-specific IgE, nasal inflammatory cells counts (mast cells, eosinophils, and T cells) and nitric oxide concentration in nasal excretion. The use of anti-allergic medication will also be recorded as one of the secondary indicators. Furthermore, adverse events will be recorded and analyzed. If any participants withdraw from the trial, intention-to-treat analysis (ITT) and per-protocol (PP) analysis will be performed.

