## Methods and design

### Study design

This study will be a double-blind, randomized, sham-controlled trial conducted in the Department of Otorhinolaryngology-head and neck surgery, Teaching Hospital of Chengdu University of T.C.M., China. This study includes the following time points: a run-in period of 4 weeks after screening, a treatment period of 4 weeks, and a follow-up period of 12 weeks. The total study period will be 20 weeks. At the screening visit, medical history especially in relation to AR and other allergic diseases will be asked and recorded by a study physician based on a systemically designed questionnaire. Patients who satisfy the inclusion criteria will be recruited into the run-in period. After randomization, patients will be blindly assigned to either the real catgut implantation at the acupoints group or the sham group (controls). All patients will receive two treatments over a period of 4 weeks. Chlorphenyramine will be used as a rescue medication if the patients present with untolerable AR symptoms. At the same time, patients should complete visual analogue scales (VAS) [9] and Rhinoconjunctivitis Quality of Life Questionnaires (RQLQ) [10,11] before randomization, at the end of treatment, during and after the follow-up period, respectively. Meanwhile, inflammatory cells and mediators in nasal secretions will also be measured at these three visits. Outcome measurements will be assessed by evaluating the efficacy and safety of catgut implantation at acupoints in the treatment of AR.

The design of this study followed the guidelines of the Helsinki Declaration (Version Edinburgh 2000) and was approved by Sichuan Regional Ethics Review Committee on Traditional Chinese Medicine (TCM). Informed consent are to be obtained from all the study patients. Before signing the consent, all patients will be given enough time to decide whether to participate in the trial. Other treatment options instead of catgut implantation at acupoints will be available for those who are unwilling to be recruited in the study.

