### Statistical analysis

In our preliminary study to compare the efficacy of catgut implantation at acupoints with intranasal glucocorticoid, it was suggested that efficiency was 93.75% in the catgut implantation group and 96.88% in the control group. In this study, we anticipate an improvement of no less than 15% after real catgut implantation at acupoints. However, there are no previous data regarding the VAS or RQLQ scores for the treatment of AR with catgut implantation at acupoints. Considering participants recruited in the two groups are in a 1:1 ratio, the following formula was used to estimate sample size [13]:

$$n_{1}=n_{2}={\left[\frac{Z_{\alpha }\sqrt{2\pi_{c}\left(1-\pi_{c}\right)}+Z_{\beta }\sqrt{\pi_{1}\left(1-\pi_{1}\right)+\pi_{2}\left(1-\pi_{2}\right)}}{\pi_{1}-\pi_{2}}\right]}^{2}$$

In the formula: n1, n2 represents the sample size of each group. π1, π2 is the overall rate of each sample, respectively. πc = (π1 + π2)/2, α = 0.05, Z_0.05_ = 1,96,β = 0.10,Z_0.10_ = 1.282. Statistical analysis will be performed using a 5% significance and 90% power, resulting in an estimated 121 patients per group.

To test our hypothesis, the first step is to assess the baseline characteristics of two groups using an unpaired *t* test or *x*^2^ testes. The second step is to compare the efficacy of real catgut implantation with the sham one, including the primary and secondary outcomes using two-sample t test. If there is any case lost in follow-up phase or withdrawn from the trial, the causes of withdrawal should be clarified. The intention-to-treat analysis (ITT) and per-protocol (PP) analysis should be conducted to test whether the result of this trial is credible. For relief medication, within-group as well as between-group comparisons of scores are to be made. Data will be analyzed using the Statistical Package for the Social Sciences software, version 15.0 for Windows (SPSS Inc., Chicago, IL, USA). Data are presented as mean and 95% confidence intervals (CI). The statistical analysis will be performed in a blinded manner by qualified statisticians.

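### VAS and RQLQ are both primary at a single 5% level, with no primary visit named and no rule on whether one or both must succeed

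*Protocol article*

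**What the plan says.** The Primary outcome section of the protocol article names two primary measures, VAS and RQLQ, without ranking them. The abstract names the same pair: "Primary indicators are subjective symptoms scores evaluated by visual analogue scales (VAS) and Rhinoconjunctivitis Quality of Life Questionnaires (RQLQ".

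Both are repeated measures. For VAS, "VAS scores will be recorded every 2 weeks during the whole trial". The RQLQ follows a four-weekly schedule, described thus: "at baseline, at the end of treatment, during the follow-up period, and at the end of follow-up period (a total of five times". The Study design section sets the time frame as "a run-in period of 4 weeks after screening, a treatment period of 4 weeks, and a follow-up period of 12 weeks". The same section also gives a coarser timetable for both scales: "before randomization, at the end of treatment, during and after the follow-up period, respectively".

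The Statistical analysis section describes the efficacy comparison thus: "compare the efficacy of real catgut implantation with the sham one, including the primary and secondary outcomes using two-sample t test". It states one 5% significance level with 90% power. Intention-to-treat and per-protocol analyses are to show whether the result is credible. No section names a primary visit, a summary over visits, an order of testing, an either-or-both rule, or an adjustment.

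**The concern.** A two-sample t test needs one value per patient. Each patient will have several VAS and several RQLQ values, so the stated test cannot be run on the stated outcome until someone picks a visit or a summary. If that choice comes after the data are seen, the 5% no longer describes the risk of a false claim. Two primary scales with an unstated success rule add to this: if either may win, the level exceeds 5% even at one visit.

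The clinical question is open too. The Background reports that, in the pilot against a nasal steroid, efficacy was similar at 4 weeks, while recurrence and symptom-free days favoured catgut after 3 months. Effect at end of treatment and durability are therefore different questions, and the article does not say which one the trial is to answer.

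The planned blinding of the analysis does not close the gap. The groups stay coded A and B until the analysis is done, but an analyst can see which visit and scale separate A from B without knowing which group is which.

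**Working it through.** **Step 1. Count the occasions.** After randomisation there are 4 + 12 = 16 weeks.
- VAS every 2 weeks: 16 / 2 = 8 occasions (weeks 2 to 16).
- RQLQ every 4 weeks: 16 / 4 = 4 occasions (weeks 4, 8, 12, 16), which with baseline makes the stated five.
- Together at most 8 + 4 = 12 outcome-by-visit cells, at no more than 8 distinct time points.
- The coarser timetable in Study design, read as three post-baseline stages for two scales, gives 2 × 3 = 6 cells.

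**Step 2. See whether the sample size identifies the primary comparison.** The article's two-proportion formula was run with π1 = 0.9375 (pilot catgut rate) and π2 = 0.9375 × 0.85 = 0.7969. This reads the 15% as relative, which is an assumption because the article does not give π1 and π2.
- πc = 0.8672; √(2πc(1 − πc)) = 0.4799; √(π1(1 − π1) + π2(1 − π2)) = 0.4695; difference = 0.1406.
- n = [(1.96 × 0.4799 + 1.282 × 0.4695) / 0.1406]² = 120.3, rounded up to 121. This matches the stated figure.
- Read as 15 absolute points (0.9375 against 0.7875), n is 109.

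The stated size can be reproduced, but it rests on a binary efficiency rate. The article says there are no earlier VAS or RQLQ data. So the power calculation points to neither scale and to no visit.

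**Step 3. False-positive rate if any p < 0.05 counts.** For k independent tests the rate is 1 − 0.95^k:
- k = 2: 9.75%
- k = 4: 18.5%
- k = 6: 26.5%
- k = 12: 46.0%

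The tests are in fact correlated. The article gives no correlations, so the ones below are assumptions. Each figure comes from 200,000 draws of correlated normal test statistics, two-sided at 1.96, with correlations from 0.9 (low end) to 0.3 (high end) over time and between scales:
- Two scales, one visit (2 tests): 7.0% to 9.5%.
- Two scales, end of treatment and end of follow-up (4 tests): 9.8% to 17.6%.
- Two scales, three visits (6 tests): about 12% to 25%.
- All 12 cells: about 15% to 42%. With autoregressive correlation 0.9 per 2-week step and 0.8 between scales, about 22%.

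**Step 4. When would the 5% hold as written?** If both scales had to reach p < 0.05 at one visit named in advance, the rate could not exceed 5%, because each test alone is held at 5%. The article states neither condition.

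**Step 5. Price of splitting the level.** On the inputs of Step 2 with 121 per group:
- At 0.05, power = Φ[(0.1406 × √121 − 1.960 × 0.4799) / 0.4695] = Φ(1.29) = 90%.
- At 0.025, power = Φ[(0.1406 × √121 − 2.241 × 0.4799) / 0.4695] = Φ(1.00) = 84%. Restoring 90% there would take 143 per group.

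**The case against.** The strongest reply is that the 12-cell count is a worst case and not the plan. This stands. The two-weekly VAS is a recording schedule, and the analysis text says only that outcomes are compared by t test. A reader might infer that a dozen primary tests will each be run at 5%, with a false-positive rate above 40%. The documents do not say that, and the larger figures need both that assumption and assumed correlations. Only the 7% to 10% figure is free of any assumption about several visits, and it still needs an either-wins rule.

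Second, the article joins the scales with a plain and, so both might be required. At one named visit that would keep the 5%. It is therefore too strong to say that the level is lost. The text supports only that it is not shown to hold.

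Third, a reader might count the per-protocol repeats as further chances of success. The article gives them a credibility role, and nothing suggests that they could carry the claim alone.

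Fourth, this is a condensed article, and the analysis plan is not shown. Details of an adjustment may properly sit there. But which outcome, at which time, under which success rule, is what a protocol fixes. This article does state its primary outcomes, its test and its level; as stated, they do not make up one defined comparison.

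**Conclusion.** The concern holds in this form: two repeatedly measured primary scales share one 5% level, with no primary visit and no either-or-both rule, so the confirmatory claim is not defined. If either scale may win, the overall false-positive rate is about 7% to 10% at one visit, about 10% to 18% if end of treatment and end of follow-up both count, and about 15% to 42% (46% if independent) if every recorded visit counts. That some inflation occurs under any either-wins reading depends only on the tests not being perfectly correlated. Its size depends on assumed correlations and on how many visits are used, which the article leaves open. With undivided 5% tests and no order, the level is assured only if both scales must succeed at one visit named in advance.

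**What to change.** Write the following into the protocol or analysis plan. Do it before unblinding and, because the codes are opened only after the analysis, before any A-versus-B comparison is run.

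1. Name one primary visit, end of treatment or end of follow-up, on the intention-to-treat set. The choice is the sponsor's, and it matters because the pilot difference appeared at follow-up and not at 4 weeks.
2. Control the two-sided 5% over the two scales at that visit by one stated rule:
   - a fixed order, for example VAS then RQLQ, each at 5%, the second tested only if the first succeeds;
   - both scales required, each at 5%; or
   - Holm.
3. Treat other visits, secondary outcomes and the per-protocol analysis as supportive, reported with 95% confidence intervals and no confirmatory claim.

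The change is wording only. Under a fixed order, the second scale cannot be claimed if the first fails. Requiring both lowers the chance of success: if each scale had 90% power, joint power would lie between 0.9 × 0.9 = 81% (independent) and 90% (fully dependent). Holm tests the smaller p-value at 0.025, where power with 121 per group is about 84%. That figure uses the protocol's binary inputs with the 15% read as relative, since the article gives no standard deviation for either scale.

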#### Secondary outcome

Secondary outcome measures include relief medication scores, serum allergen-specific IgE, nasal inflammatory cells counts (mast cells, eosinophils, and T cells), the level of nitric oxide concentration in nasal secretion, and side effects.

Patients will be asked to complete diaries in the baseline and every 2 weeks after randomization. In the diaries, they will document the intensity, frequency, length, and symptoms in each AR attack. The patients will also record if H1-blocker (chlorphenyramine) has been taken during the whole treatment periods, including the dosage and time of medication. In addition, adverse events (for example, numbness, hematoma, local infection of the acupuncture sites, headache, fainting, and serious pain) will also be recorded during the treatment and follow-up phases.

### Patient safety

Before randomization, patients will be asked to undergo routine tests of blood, urine, and stool, as well as electrocardiogram (ECG), liver function, hepatitis serology, serum antibody of AIDS, blood glucose, and kidney functions in order to exclude any related serious illness. The results of these tests will allow the assessment of risks associated with catgut implantation at acupoints. If any adverse effect occurs during the trial, patients will contact with the principal investigator as soon as possible to get proper medical treatment.

